## Methods

### Study Design

This prospective cohort study will be conducted at a university hospital that provides specialized asthma treatment. The study protocol was developed following the SPIRIT (Standard Protocol Items: Recommendations for Interventional Trials) checklist guidelines [14], and the trial was registered at ClinicalTrials.gov (NCT05159076). The study design is illustrated in Figure 1. Individuals with asthma will be enrolled in the trial after a routine medical consultation. Baseline lung function will be checked from the medical records. Eligible participants will undergo an 8-week behavioral intervention protocol to increase PADL and reduce sedentary behavior. First, all included individuals will receive an educational program, followed by an intervention aimed at increasing physical activity. All individuals will be assessed before and after the 8-week intervention and then 16 weeks later. The outcomes assessed will include anthropometric variables, clinical asthma control, health-related quality of life, physical activity levels, anxiety and depression symptoms, exacerbations, body composition, barriers to performing PADL, and physical activity behavioral stages (Figure 1).

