### Participants

The study will include both male and female adults aged 18 to 65 years with moderate to severe asthma [1] who are not physically active (<150 min of moderate to vigorous physical activity/wk [15] or ≤7500 steps/d) and have partially controlled or uncontrolled asthma (Asthma Control Questionnaire [ACQ] score ≥0.75) [16]. In addition, the following inclusion criteria will be considered: diagnosis of asthma based on the recommendations established by GINA [1], outpatient medical treatment for at least six months, and a stable clinical status for at least 30 days (no hospitalizations, visits to emergency services, or medication changes) [17]. Pharmacotherapy will be maintained throughout the intervention period. After being informed about the possible risks and benefits of the study, participants will be instructed to sign an informed consent form.

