**Assessments:**						
	Lung function			✓		
	PADL^a^ and sedentary behavior	✓			✓	✓
	Asthma Control	✓			✓	✓
	Asthma exacerbations			✓	✓	✓
	Quality of life			✓	✓	✓
	Anxiety and depression			✓	✓	✓
	Barriers to perform PADL			✓	✓	✓
	Behavioral stage for PADL			✓	✓	✓
	Anthropometric data			✓	✓	✓
	Body composition			✓	✓	✓

^a^PADL: physical activity in daily life.

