### Outcome Measures

The primary outcome will be PADL (the number of steps per day) using an activity monitor (by actigraphy). Secondary outcomes will include clinical asthma control, quality of life, body composition and anthropometric data, anxiety and depression levels, asthma exacerbations, physical activity barriers, and behavioral stages for physical activity. This will be a single-blinded (outcome assessor) study in which assessments will be performed before, immediately after, and 16 weeks later.

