### Statistical Analysis Planning

Individuals will be stratified as “responders” and “nonresponders” based on an increase of ≥2500 steps [45]. The Kolmogorov-Smirnov test will be used to assess data normality. Cluster analysis will be used to characterize the groups according to individual characteristics. Cluster analysis will be carried out in 2 stages: hierarchical analysis using the Ward method to determine the number of clusters and k-means analysis to group the clusters [46]. Comparisons of clinical, anthropometric, and psychosocial data obtained in the responder and nonresponder groups will be conducted using the 2-tailed *t* test or Mann-Whitney *U* test for continuous variables and the chi-square test for categorical variables. To determine the independent factors associated with the level of PADL (dependent variable, considering clinical control, smoking, obesity, anxiety, and depression as independent variables), multiple linear regression analysis (stepwise forward) will be used. The intra- and between-group comparison at baseline, short term, and medium term will be assessed using the 2-way ANOVA with repeated measures test. The significance level will be adjusted to 5% (*P*<.05) for all tests. If necessary, intention-to-treat analysis will be performed, as described earlier. SPSS Statistics (version 22.0; IBM Corp) will be used for statistical analysis. Data integrity will be monitored by regularly scrutinizing data files for omissions and errors. Participants will be given an anonymous study ID to protect confidentiality, and only study investigators will have access to the final trial data set.

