### Strengths and Limitations of the Study

In addition to the potential to identify the characteristics of responders and nonresponders, this study will also follow up 4 months after training, considered the medium term. These results will allow us to determine if behavioral changes are maintained in the responders over time. The assessment of PADL using accelerometers as a primary outcome is a study strength because it is an objective outcome measure, thus decreasing the risk of bias. The fact that the study will be performed in only 1 hospital center can be considered a limitation.

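### Exacerbations accrue over an 8-week and then a 16-week interval, but the only method stated for change over time is a repeated-measures ANOVA with no allowance for time at risk

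*Protocol article*

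**What the plan says.** - **Outcome.** Outcome Measures includes among the secondary outcomes "anxiety and depression levels, asthma exacerbations, physical activity barriers, and behavioral stages for physical activity". In Table 2 the row "Asthma exacerbations" is ticked at baseline, 8 weeks and the 16-week follow-up.
- **Timing.** Study Design: "All individuals will be assessed before and after the 8-week intervention and then 16 weeks later". Strengths and Limitations agrees: "this study will also follow up 4 months after training, considered the medium term". The two on-study intervals are therefore 8 and 16 weeks.
- **Definition.** The Asthma Exacerbations section defines an event by any one of several criteria: heavy rescue use over 48 hours, systemic corticosteroids, an unscheduled appointment, or an emergency visit or admission.
- **Entry.** Participants must have had "a stable clinical status for at least 30 days (no hospitalizations, visits to emergency services, or medication changes").
- **Analysis.** Statistical Analysis Planning says that comparison within and between groups over the three time points "will be assessed using the 2-way ANOVA with repeated measures test". The other tests there, the t test or "Mann-Whitney *U* test for continuous variables and the chi-square test for categorical variables", are assigned to the comparison of responders with nonresponders.
- **Not stated.** The article does not give the period over which exacerbations are counted at each visit, the baseline look-back, or the scale (count, yes/no or rate).

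**The concern.** A repeated-measures ANOVA compares means that are on the same footing at every visit. That suits daily steps or a questionnaire score. An exacerbation is an event that accrues over time, so a count since the last visit grows with the length of the interval. Put into the stated ANOVA, an unchanged rate can appear as a change over time.

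The counts are also sparse, which suits ANOVA poorly. The entry criterion, moreover, removes many of the defining events from the month before the study.

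The second objective is to evaluate functional and clinical benefit in the medium term. There is no control arm, so within-group change over time carries that objective, and it is the comparison affected. A false rise after the programme would read as loss of benefit. A false fall from a long baseline look-back would read as benefit.

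**Working it through.** **Inputs from the document.** Intervals of 8 and 16 weeks (Study Design); N = 100 and 17% nonresponders (Sample Size Calculation), hence a 17/83 split; 5% significance level (Statistical Analysis Planning). The plan has no figure for exacerbations to reproduce. Its own group size does reproduce: a difference of 2500 with SD 2500, two-sided 5% and 80% power, needs 16.7, so 17, per group by the t test, and 17/0.17 = 100. That figure does not bear on this point.

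**Assumptions.** Annual rate r of 0.5, 1 or 2 per patient, constant over time; patient-level variation by a gamma frailty with mean 1 and variance 1; events counted since the previous visit.

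**Step 1: expected counts.** Mean = r × weeks/52.

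| r per year | 8 weeks | 16 weeks |
|---|---|---|
| 0.5 | 0.077 | 0.154 |
| 1 | 0.154 | 0.308 |
| 2 | 0.308 | 0.615 |

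The ratio is 2 at every rate.

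**Step 2: 8-week versus 16-week counts.** The within-patient difference has mean r(8/52) and variance r(24/52) + r²(8/52)². At r = 1 the mean is 0.154 and the variance 0.4615 + 0.0237 = 0.485, so SD = 0.697 and, with 100 patients, z = 0.154/0.0697 = 2.21. The chance of p < 0.05 is about Φ(2.21 − 1.96) = 0.60. Simulation with a paired t test (4,000 runs) gives 33%, 61% and 88% at r = 0.5, 1 and 2.

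**Step 3: the three-visit ANOVA as stated.** Mixed two-way ANOVA with Greenhouse-Geisser correction, 17/83 split, 2,000 runs. False time effects at nominal 5%:

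| Baseline window (assumed) | r = 0.5 | r = 1 | r = 2 |
|---|---|---|---|
| 30 days, full rate | 35% | 62% | 92% |
| 30 days, half rate | 46% | 83% | 99% |
| 30 days, almost no events | 65% | 96% | 100% |
| 12 months (baseline is the highest count) | 98% | 100% | 100% |
| 8 weeks at all three visits | 4.4% | 4.1% | 4.3% |

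The group-by-time test stays between 3.9% and 5.9% throughout when both groups share a rate.

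**Step 4: with person-time.** Given the total number of events, the 8-week share at a constant rate is 8/24 = 1/3. A binomial test of that share rejects in 3.4%, 4.4% and 4.2% of runs. ANOVA on annualised rates, with one true rate in all three windows (30 days, 8 weeks, 16 weeks), rejects for time in 4.9%, 5.9% and 5.4%. The unequal windows are therefore the cause.

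**Step 5: a yes/no version.** With the same frailty, the chance of at least one event is m/(1 + m), where m is the expected count. At r = 1 this is 0.154/1.154 = 13% over 8 weeks and 0.308/1.308 = 24% over 16 weeks. Dichotomising does not remove the dependence on window length.

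**Step 6: the entry criterion.** The 30 days exclude admissions, emergency visits and medication changes. They do not exclude the rescue-use criterion, nor clearly an unscheduled appointment. If the baseline look-back were 8 weeks, the stable period would fill 30/56 = 54% of it. Scaling to a rate does not repair this depletion.

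**The case against.** The ANOVA sentence names no outcome and cannot cover every secondary outcome, because behavioral stage is to be presented as frequencies. The definition could be read as yes/no rather than a count. Visit spacing is not a recall period, and a journal article may leave the counting window to the full protocol. Equal windows would remove the artefact.

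Most of this stands, and it rules out three stronger readings:

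- *That the plan as written will show a rise after the programme.* This needs counting since the last visit, which is not stated. Even then, about two thirds of trials at 0.5 per year show no significant change.
- *That the intervention period will show a rise over an artificially quiet baseline.* No baseline window is given. The stable month is event-poor, not event-free, and a 12-month look-back reverses the direction.
- *That the comparison of responders with nonresponders over time is distorted.* Under a common rate it is not.

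The choice of method is not removed by the objection. The article does state a longitudinal method, exempts no outcome by name in that sentence, and gives no alternative for exacerbations that allows for exposure. Step 5 shows that a yes/no reading has the same dependence on window length.

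**Conclusion.** The point holds in conditional form and should be corrected. The only longitudinal method stated takes no account of time at risk and suits sparse events poorly, while the on-study intervals differ twofold.

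If exacerbations enter that ANOVA as counts since the previous visit, a constant rate gives a false difference between the two on-study intervals in roughly 33% to 88% of trials. This assumes 0.5 to 2 exacerbations per patient-year, the stated frailty and 100 patients. The error is confined to within-group change over time in one secondary outcome. It does not touch the primary outcome or, under a common rate, the responder-by-time test.

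A baseline artefact is also possible, but its size and direction cannot be fixed from the document.

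**What to change.** - Take exacerbations out of the repeated-measures ANOVA and state the counting window for each visit.
- Compare the 8-week and 16-week periods as a rate per patient-week, using a Poisson or negative-binomial model fitted by GEE, with the log of each patient's weeks at risk as offset. Equal counting windows are an acceptable alternative, at the price of not using the events outside the shorter window.
- Do not test change against a baseline window that includes the 30 stable days. Report any baseline exacerbation history already collected descriptively, or use it as a covariate. No new chart-based look-back is needed.

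The cost is analysis wording. The rate model needs only the events and weeks of observation in the two study periods and can be fitted in SPSS, the package the plan names. Equal windows would also need event dates.

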The World Health Organization (WHO) recommends that adults perform 150 to 300 minutes of moderate-intensity aerobic physical activity weekly to achieve certain health benefits [8]. In addition, international guidelines [9] and GINA [1] classify, with A-level evidence, people with asthma who engage in regular physical activity to reduce cardiovascular risk and improve their quality of life [1]. A previous study found that a behavioral intervention to increase PADL improves clinical asthma control, sleep quality, and anxiety symptoms in adults with moderate to severe asthma [5]. However, 17% of the individuals did not improve their physical activity level, and 25% did not improve their clinical control after the intervention. Individuals with other chronic respiratory [10], cardiac [11], musculoskeletal [12], and neurological diseases [13] have also been classified as better or worse responders to specific interventions.

Thus, despite the benefits obtained by behavioral intervention aimed at increasing PADL in adults with asthma [5], it is necessary to know the characteristics of responders and nonresponders to guide the management in a more personalized approach. Moreover, the effects of this intervention were only assessed in the short term (immediately after the intervention), and the medium-term effects remained unknown. We hypothesize that the intervention might cause different effects according to the clinical characteristics of the individuals, including asthma control, age, anxiety and depression levels, obesity, and several comorbidities. Therefore, the main objective this prospective cohort study will be to identify the characteristics of adult responders and nonresponders with moderate to severe asthma to a behavioral intervention to increase PADL and evaluate the functional and clinical responses in the short and medium terms.

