### Sample Size Calculation

A minimum number of 17 individuals in at least one of the groups (responder or nonresponder) was established to detect a difference of 2500 (SD 2500) steps [45] in the primary outcome (α=5%, 1 – β=80%). A sample of 100 participants was established, considering the percentage of nonresponders (17%) as previously observed [5]. Clinical improvement in the ACQ score (≥0.5) [3,32] will be considered a secondary outcome.

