### Contribution and Clinical Applicability

To our knowledge, this will be the first study to assess the characteristics of responders and nonresponders to a behavioral intervention aimed at increasing PADL in adults with asthma. Therefore, the results obtained in the proposed protocol may provide vital information for health care professionals to refer patients with asthma to more specific intervention approaches (behavioral or otherwise) based on their profile as potential responders or nonresponders. Furthermore, this study may clarify whether the potential gains obtained in the short term after the intervention are maintained in the medium term in individuals with moderate to severe asthma.

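### Responder and nonresponder characteristics are each tested at an unadjusted 5%, with no analysis named as deciding objective 1 and none called exploratory, yet the conclusions promise guidance for prescribing

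*Protocol article*

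**What the plan says.** The Objective (Abstract) and the Introduction make identifying the characteristics of responders and nonresponders the main aim. The Introduction gives this hypothesis: "the intervention might cause different effects according to the clinical characteristics of the individuals, including asthma control, age, anxiety and depression levels, obesity, and several" (its list of factors ends with comorbidities).

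Under Statistical Analysis Planning:

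- Groups: "Individuals will be stratified as “responders” and “nonresponders” based on an increase of ≥2500 steps".
- Tests: "Comparisons of clinical, anthropometric, and psychosocial data obtained in the responder and nonresponder groups will be conducted using the 2-tailed" (for continuous variables a t test or Mann-Whitney; for categorical variables chi-square).
- Other analyses: a Ward and k-means cluster analysis to characterise the groups, and a forward stepwise linear regression of PADL level on clinical control, smoking, obesity, anxiety and depression.
- Threshold: "The significance level will be adjusted to 5% (*P*<.05) for all tests".

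No comparison is ranked or called exploratory. On use of the result, Contribution and Clinical Applicability says it "may provide vital information for health care professionals to refer patients with asthma to more specific intervention approaches" according to responder profile. The Conclusions of the Abstract and of the Discussion go further and say that identifying these individuals will help clinicians prescribe specific interventions.

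**The concern.** The word adjusted in the threshold sentence describes no multiplicity adjustment. It sets 5% for each test, whatever their number. This is a stated rule, so it cannot be treated as a detail left to an analysis plan that is not shown.

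The primary outcome does not settle which analysis decides. Steps per day define the groups, so they cannot also be the characteristic under test. The three analyses can produce three different lists: the clusters are formed without regard to a per-variable P value, the univariable tests look at one variable at a time, and the regression models activity level and not responder status. Its covariates also leave out age and comorbidities, which the hypothesis names.

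At stake is the content of the main result. A chance difference could be reported as a feature of nonresponders and then used to decide who is referred to the programme.

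**Working it through.** **1. The plan's own figures.** Sample Size Calculation is set "to detect a difference of 2500 (SD 2500) steps" with "α=5%, 1 – β=80"%. The standardised difference is 2500/2500 = 1.0. A two-sided, equal-group t test needs 16.7, so 17 per group, and 17/0.17 = 100. Both figures reproduce. They concern steps per day, so no characteristic was used to size the study.

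**2. How many comparisons.** The protocol gives no number. From the measures it names:

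| Domain | Variables | Count |
|---|---|---|
| Clinical | ACQ, AQLQ total, exacerbations, lung function | 4 |
| Anthropometric | weight, BMI, three circumferences, waist-to-hip ratio | 6 |
| Body composition | fat mass, fat-free mass, visceral adiposity area, skeletal muscle mass | 4 |
| Psychosocial | HADS anxiety, HADS depression, barriers, behavioural stage | 4 |
| Other | age, smoking | 2 |
| Total | | 20 |

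Adding height gives 21. The AQLQ domains, sex or accelerometer measures would raise it further. Smoking appears in the protocol only as a regression covariate, so the count could also be slightly lower.

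**3. Chance of at least one false positive when nothing predicts response.** For k independent tests at 5% it is 1 − 0.95^k. For k tests with common correlation ρ it is

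1 − ∫ φ(z) [Φ((c − √ρ z)/√(1−ρ)) − Φ((−c − √ρ z)/√(1−ρ))]^k dz, with c = 1.96.

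| k | ρ = 0 | ρ = 0.5 | ρ = 0.8 |
|---|---|---|---|
| 20 | 64.2% | 41.9% | 22.4% |
| 6 | 26.5% | 20.7% | 13.9% |

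The row for six corresponds to testing only the hypothesised factors (asthma control, age, anxiety, depression, obesity, comorbidities). The expected number of false positives among 20 is 20 × 0.05 = 1.0 at any correlation.

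**4. A correlation pattern closer to the data.** I simulated t tests at 17 versus 83 with 20 variables in blocks: nine body-size, five quality-of-life, two HADS and four single. Correlation was 0.7 to 0.9 within blocks and 0.1 to 0.2 between them. The chance of at least one false positive was 40% to 49%. These correlations are assumptions.

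**5. What a confirmatory adjustment would cost.** Two-sample t test, 17 versus 83, 80% power:

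| Per-test level | Detectable difference |
|---|---|
| 0.05 | 0.75 SD |
| 0.05/6 = 0.0083 (first Holm step, six factors) | 0.94 SD |
| 0.05/20 = 0.0025 (Bonferroni, 20 tests) | 1.05 SD |

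At the first Holm step on six factors, power at 0.75 SD falls from 80% to about 55%, and power at 0.5 SD from 46% to 21%.

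**The case against.** The strongest reply is that this is an uncontrolled, single-centre cohort, described as the first of its kind, whose purpose is to find candidate characteristics. Many statisticians would not require familywise control there, and with about 17 nonresponders an adjustment hides real predictors as well as false ones. There is some prespecification: the regression is limited to five covariates, four of them on the hypothesised list. An article may also leave a hierarchy to a fuller plan.

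Much of this stands. It argues against imposing an adjustment. It does not rescue a flat 5% rule combined with conclusions about prescribing, because the case for unadjusted searching rests on calling it a search.

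Four stronger readings are tempting and should be resisted:

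- *A false characteristic is likely.* Only at low correlation does the chance exceed one half. Half of the 20 variables are body-size or body-composition measures, and lung function is already an ACQ item, so low correlation throughout is implausible. One false positive is a mean; at correlation 0.5 the chance of none is 58%.
- *The plan breaches its own 5% by a large factor.* It states a per-test level and never claims a familywise 5%.
- *Any variable with P<.05 is declared a characteristic.* The document gives no such rule; it leaves the reader without one, and the cluster analysis yields no per-variable P value.
- *About 20 baseline variables are tested.* The protocol gives neither that number nor the word baseline for these comparisons. Baseline is the natural reading for predictors of response, but it is a reading.

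**Conclusion.** The concern holds as a mismatch between the stated testing rule and the claims built on it. Each characteristic is tested at an unadjusted 5%, nothing says which of three analyses answers objective 1, nothing is labelled exploratory, and the conclusions speak of prescribing.

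Under the complete null, the chance of at least one false characteristic is about 42%, with a range of 22% to 64%. This rests on a count of about 20 variables and on assumed common correlations from 0.8 down to 0. The tests within the regression and the repeated-measures ANOVA are not counted.

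The power figures also rest on the 17/83 split. That split is uncertain: the 17% is described in the Introduction as those whose activity level did not improve, which is not the same as gaining fewer than 2500 steps.

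**What to change.** In Statistical Analysis Planning, replace the blanket 5% rule for these comparisons with a statement that:

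- the univariable comparisons, the cluster analysis and the stepwise regression are exploratory;
- group comparisons are reported as differences with 95% confidence intervals, and P<.05 alone does not identify a characteristic;
- the hypothesised factors that the study measures (asthma control, age, anxiety, depression, obesity) are listed first and separately from all other variables.

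Reword the Conclusions of the Abstract and of the Discussion as hypothesis-generating. Comorbidities are left off the list because neither the assessment schedule nor the outcome sections include them; they could be added once a measure is defined.

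The cost is a more modest conclusion. No new data or patients are needed, and the article reports recruitment and data collection as ongoing.

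If the authors want a confirmatory claim, they should confine it to those measured factors, define each one (obesity has no stated cut-off) and specify an adjustment such as Holm or false discovery rate control. They must then accept lower power. Holm on six factors raises the detectable difference at 17 versus 83 from 0.75 SD to as much as 0.94 SD; with five factors the first step is less strict, so the loss is a little smaller.
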